##### Short intracortical inhibition (SICI) and intracortical facilitation (ICF)

Paired pulse TMS (pTMS, Xiang Yu Medical; China) will be used to measure short intracortical inhibition (SICI) and intracortical facilitation (ICF), both of which are important indicators for evaluating the plasticity of the cerebral cortex. Building upon the preceding procedures, SICI and ICF entail a stimulation at 80% of the resting threshold (RT), a second stimulation at 120% of RT, and an interstimulus interval (ISI) of 3 ms and 12 ms, respectively [38]. Similar to the MEP assessment, each parameter will be subjected to five stimulations to calculate the average value. All the TMS procedures mentioned above will be completed by a professional physiotherapist with 5 years of clinical experience [39].

##### Magnetic resonance imaging (MRI)

MRI (3-T Siemens Skyra, Erlangen Germany) with a circular surface coil will be used to explore changes in the brain, including gray matter density, cortical thickness, subcortical nuclei volumes, and functional connectivity. Each participant will undergo an MRI scan for approximately 25 min, performed with their eyes closed and extra padding around the ears to reduce noise interference during the MRI scanning process.

Four distinct scanning sequences will be implemented as follows: (1) Resting-state functional MRI images (rs-fMRI): recurrence time (TR) = 2100 ms, echo time (TE) = 30 ms, flip angle = 90°, voxel size = 0.9 isotropic, 42 axial slices, field of view (FOV) = 200 mm × 200 mm, and phases = 230. (2) High-resolution T1-weighted structural images (T1WI): TR = 8.2 ms, TE = 3.2 ms, flip angle = 12°, FOV = 220 mm × 220 mm, matrix = 256,256, slice thickness = 1 mm [40]. (3) Blood oxygenation level-dependent (BOLD) signal: TR = 2000 ms, TE = 30 ms, flip angle = 90°, FOV = 240 mm × 240 mm, thickness = 4 mm, no interval scanning. (4) Diffusion tensor imaging (DTI): TR = 3800 ms, TE = 106 ms, FOV = 230 mm × 230 mm, apply dispersion gradients and 1 no dispersion weight vegetable chicken in 20 directions, where B = 1000 s/mm^2^.

##### RNA-sequencing of the blood sample

Every participant will undergo the collection of a 1-mL blood sample from a vein by a skilled nurse, both at baseline and following 2 weeks of the tACS intervention period. The aim is to discern alterations in neuroinflammatory factors, nerve growth factors, and synaptic plasticity-related genes in the blood milieu [41]. Participants will be instructed to abstain from food consumption after 20:00 the previous evening, along with refraining from drinking and high-intensity exercise prior to the blood draw. Additionally, breakfast consumption will be prohibited on the day of the blood sampling. After emptying the bladder, participants will proceed to a laboratory room. A volume of 1 ml venous blood will be collected into an EDTA anticoagulant tube. To this, 3 ml of TRIzol Reagent (LMAl Bio, China) will be added, ensuring thorough mixing. Subsequently, the mixture will be incubated at 25 °C for a duration of 5 min, after which it will be stored at − 80 °C [41]. This meticulous process facilitates the preservation and stability of the blood samples for subsequent biochemical analysis.

### Participant timeline {13}

The time schedule of enrolment, interventions, assessments, and visits for participants is shown in Table 1.

### Sample size {14}

The sample size calculation was conducted using G*power software (v3.1.9.2). The effect size of this study was estimated from a study conducted by Jaberzadeh et al. who investigated the differential effects of unihemispheric concurrent dual-site and conventional tDCS on motor learning using SRTT [11], which was determined to be 0.526. According to a prior two-way analysis of variance (ANOVA) F test, with a power of 0.95 and an alpha (α) level of 0.05, an estimated 32 participants will be needed. Considering a 20% drop-out rate, the final sample size of each group will be 10, with a total of 39.

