## Abstract

**Background:**

Transcranial alternating current stimulation (tACS) has proven to be an effective treatment for improving cognition, a crucial factor in motor learning. However, current studies are predominantly focused on the motor cortex, and the potential brain mechanisms responsible for the therapeutic effects are still unclear. Given the interconnected nature of motor learning within the brain network, we have proposed a novel approach known as multi-target tACS. This study aims to ascertain whether multi-target tACS is more effective than single-target stimulation in stroke patients and to further explore the potential underlying brain mechanisms by using techniques such as transcranial magnetic stimulation (TMS) and magnetic resonance imaging (MRI).

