## Trial design {8}

This study will be a randomized controlled trial utilizing a parallel-group design. A total of 39 stroke patients will be assigned to three groups: the sham tACS group (SS group), single-target tACS group (ST group), and multi-target tACS group (MT group) at a 1:1:1 ratio as determined by a simple random sampling process. The comprehensive study flowchart is depicted in Fig. 1, while the study schedule is outlined in Table 1. The protocol was approved by the Ethics Committee of Shanghai Seventh People’s Hospital (2023-7th-HIRB-043) and will be conducted in accordance with the ethical standards of the Declaration of Helsinki. The protocol has been registered in the Chinese Clinical Trial Registry (ChiCTR2300073465) and used the SPIRIT reporting guidelines [26]. Prior to participating in the experiment, patients will be required to provide informed consent.

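### The sample-size sentence gives 10 per group but 39 in total across three arms, and the stated 0.95 power is for an omnibus F test, not for multi-target versus single-target

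*Protocol article*

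**What the plan says.** Sample size {14} takes its effect size from a study of "differential effects of unihemispheric concurrent dual-site and conventional tDCS on motor learning using SRTT". The value reported is 0.526, and the metric is not named. The calculation is for a two-way ANOVA. Its result is stated in these terms: "with a power of 0.95 and an alpha (α) level of 0.05, an estimated 32 participants will be needed". The section then closes with the group size and the total: "Considering a 20% drop-out rate, the final sample size of each group will be 10, with a total of 39".

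Elsewhere the total is consistent. Trial design {8} says "A total of 39 stroke patients will be assigned to three groups", and the ratio given there is 1:1:1. The abstract's Methods paragraph and Sequence generation {16a} repeat 39 at the same ratio.

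The abstract puts the main question as a contrast of the two active arms: "This study aims to ascertain whether multi-target tACS is more effective than single-target stimulation in stroke patients". Objectives {7} poses the same hypothesis. The statistical methods section {20a} plans a two-way repeated-measures analysis and leaves pairwise comparisons to post hoc tests, Bonferroni-corrected where needed. The abstract lists four assessments, T0 to T3. No power is stated for any pair of arms.

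**The concern.** Two consecutive sentences hold numbers that cannot all be true. Neither text extraction nor the condensing of a full protocol into an article explains that. If 10 per arm were followed, the trial would enrol 30, fewer than its own calculation requires even with no losses. After 20% loss it would keep 24.

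The second issue is what the 0.95 describes. An omnibus F test asks whether the three arms differ somewhere. The trial's leading question is whether MT beats ST. A reader who carries the 0.95 over to that contrast could take a non-significant MT–ST result as good evidence of no difference, which the design may not support.

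**Working it through.** **Inputs.** From Sample size {14}: effect size 0.526, alpha 0.05, power 0.95, N = 32, drop-out 20%, 10 per group, total 39. From Trial design {8} and Sequence generation {16a}: three arms, 1:1:1. From the abstract: four visits. Assumed here, because not stated: 0.526 is Cohen's f, and the within-person correlation ρ lies between 0.3 and 0.7.

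**1. Head count.** 3 × 10 = 30; 39 / 3 = 13. And 30 is less than both 32 and 39.

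**2. Drop-out.**
- 32 × 1.2 = 38.4, rounded up to 39, which is the plan's total.
- Keeping 32 after 20% loss needs 32 / 0.8 = 40, or 42 for equal arms.
- 39 × 0.8 = 31.2, which is 0.8 of a participant short. 39 − 32 = 7 losses, and 7 / 39 = 18%.
- At 10 per arm: 30 × 0.8 = 24.

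**3. Reproducing the 32.** Power is from the noncentral F distribution. For the between-group effect over m visits in k groups, λ = f²·N·m / (1 + (m − 1)ρ), with k − 1 and N − k degrees of freedom. N needed for power 0.95 at f = 0.526:

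| Setting | N |
|---|---|
| Three arms, between-group, 2 visits, ρ = 0 | 32 |
| Three arms, between-group, 3 visits, ρ = 0.3 | 33 |
| Three arms, between-group, 4 visits, ρ = 0.3 | 30 |
| Three arms, between-group, 4 visits, ρ = 0.5 | 39 |
| Three arms, between-group, 4 visits, ρ = 0.7 | 47 |
| Three arms, group-by-time, 4 visits, SPSS effect-size option | 31 |
| Three arms, group-by-time, 4 visits, G*Power default option, ρ = 0.5 | 12 |
| Two groups, between-group, 4 visits, ρ = 0.5 | 32 |
| Three arms, single measurement | 59 |

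Several different settings give 32 or close to it, so the figure cannot be traced to one of them.

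**4. Three-arm omnibus power at N = 31** (39 less 20%), four visits:
- Between-group effect: 0.96 at ρ = 0.3, 0.89 at ρ = 0.5, 0.81 at ρ = 0.7.
- Group-by-time: 0.957 under the SPSS option with λ = f²(N − k)(m − 1); above 0.99 under the default option at ρ = 0.5.

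**5. MT versus ST at 13 per arm, before drop-out.** A three-arm f does not fix this gap; a pattern of means must be assumed.
- Evenly spaced, ST in the middle: d = f·√6/2 = 0.644.
- Only MT differs, ST equal to sham: d = 3f/√2 = 1.116.
- For the mean of four visits at ρ = 0.5 the variance factor is (1 + 3 × 0.5)/4 = 0.625, so d is divided by √0.625, giving 0.815 and 1.411.

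Two-sided two-sample t power (noncentral t):

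| Pattern | Outcome | α = 0.05 | α = 0.05/3 = 0.0167 |
|---|---|---|---|
| Evenly spaced | one visit | 0.35 | 0.20 |
| Evenly spaced | mean of four | 0.51 | 0.33 |
| Only MT differs | one visit | 0.78 | 0.61 |
| Only MT differs | mean of four | 0.93 | 0.84 |

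**The case against.** It can be argued that 39 at 1:1:1 appears everywhere else, so 10 per group is a slip, or means completers (13 × 0.8 = 10.4). The first is probably right, and nothing outside this sentence suggests that recruitment would stop at 30. But the sentence is still wrong as written, and three arms of 10 completers would be 30, still below 32.

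A reader might infer that the 0.95 does not apply to the three-arm design, or that the 32 came from a two-group calculation. The document supports neither. One two-group setting gives exactly 32, and with three arms that same setting has power 0.90 at 32 and needs 39. But other three-arm settings also give 30 to 33, including ones that fit the planned repeated-measures analysis. The single-measurement figure of 59 does not describe that analysis. Full software settings may also sit in a longer protocol that is not shown.

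On MT versus ST, the counter-argument is that the low values depend on the assumed means, one visit and full Bonferroni adjustment, and that the trial also asks whether 40-Hz stimulation works at all, which the omnibus test partly addresses. This stands in part. At ρ = 0.3, with only MT differing, the mean of four visits gives 0.98 unadjusted and 0.93 adjusted. If 0.526 were a two-group f (d = 2 × 0.526 = 1.05), the mean of four visits at ρ = 0.5 gives 0.90 and 0.79. So the contrast is not underpowered under every assumption. What remains is that the stated 0.95 is not a statement about this contrast.

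**Conclusion.** The contradiction is certain and rests on no assumption: 10 per group cannot stand beside 39 in three equal arms or beside 32 needed. Thirteen is the likely intended figure. The drop-out shortfall at 39 is under one participant; it would be serious (24 against 32) only if 10 per arm were really meant.

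The 0.95 for 32 can be neither confirmed nor refuted for three arms, because the tested effect, number of groups, visits, correlation and metric of 0.526 are not given.

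The 0.95 does not transfer to MT versus ST. All eight scenarios tabulated for that contrast fall below 0.95, from 0.20 to 0.93, and losses would lower them further. That range assumes that 0.526 is a three-arm f and that the mean patterns are as stated; for the four-visit rows it also assumes ρ = 0.5. A lower correlation with the most favourable pattern can exceed 0.95 without adjustment. The correction to the per-group figure is needed; the size of the power gap is conditional on these assumptions.

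**What to change.** 1. Replace the final sentence of Sample size {14} with: *13 per group, 39 in total; 32 evaluable allows 7 drop-outs (18%).*
2. State that the 0.95 refers to the omnibus F test, and under which settings: tested effect, number of groups and visits, assumed correlation, and the metric of 0.526.
3. State the power for MT versus ST separately, with the assumed pattern of means and the alpha used. If it is low, report that contrast as an estimate with a confidence interval.

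This is a change of wording and adds no patients. The only downside is that the stated power may become less favourable.

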### Recruitment {15}

Stroke patients for this study will be recruited from the neurology department of Shanghai Seventh People’s Hospital in China. The recruitment strategy will encompass a variety of methods, including posters, online advertisements, and leaflet distribution. Clear communication regarding the specifics of the experiment will be established with potential participants. Upon the voluntary endorsement of the informed consent by the patients, they will be invited to participate in the study.

## Assignment of interventions: allocation

### Sequence generation {16a}

A total of 39 eligible participants will be assigned to three groups at a 1:1:1 ratio using stratified randomization with sex, age, and stroke severity as factors in this study. The stratified randomization will be achieved as follows: Firstly, participants will be divided into men and women two groups. Secondly, the two groups will be grouped by age (< 60 and ≥ 60). Lastly, the four groups will be grouped by Brunnstrom scale grade (III, IV, V), a total of 12 subgroups. Finally, all 12 groups will be regrouped into three new groups including the SS group, ST group, and MT group to minimize the bias of the final results. The random number will be generated by Microsoft Excel (https://www.microsoft.com) and will be overseen by an external statistician who is not directly involved in the study.

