### Implementation {16c}

The envelopes will be unveiled by an independent researcher only after all participants have concluded the baseline assessments to avoid bias.

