## Trial status

Participant recruitment will start in February 2024 and is expected to be completed at the end of April 2024. The version of this protocol is the 2nd version.

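### Two sections name incompatible allocation methods; 12 strata for 39 patients do not secure 1:1:1 or severity balance under one-at-a-time allocation, and the envelope rule leaves the timing unclear

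*Protocol article*

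**What the plan says.** Trial design {8} of the Protocol article fixes the split "at a 1:1:1 ratio as determined by a simple random sampling process". Sequence generation {16a} states "A total of 39 eligible participants will be assigned to three groups at a 1:1:1 ratio", but "using stratified randomization with sex, age, and stroke severity as factors in this study". It then lists the steps: divide by sex, divide by age at 60, and then "Lastly, the four groups will be grouped by Brunnstrom scale grade (III, IV, V), a total of 12 subgroups". The closing step is "Finally, all 12 groups will be regrouped into three new groups including the SS group, ST group, and MT group". On the source of the sequence it says "The random number will be generated by Microsoft Excel", overseen by an external statistician. No rule for keeping the arms level within a subgroup is named.

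Concealment mechanism {16b} gives each participant a sealed envelope. Implementation {16c} says when these are opened: "The envelopes will be unveiled by an independent researcher only after all participants have concluded the baseline assessments to avoid bias". Trial status gives the calendar: "Participant recruitment will start in February 2024 and is expected to be completed at the end of April 2024". Eligibility criteria {10} admit patients from 2 weeks to 6 months after stroke, and the intervention lasts 2 weeks.

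**The concern.** There are three linked problems.

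- **Method.** Simple randomization ignores patient characteristics; stratified randomization is built on them. A site cannot carry out both, and the trial report could not describe the method consistently.
- **Number of strata.** Stratifying balances the arms only if the sequence within each stratum is restricted and the strata are large enough to complete most of their blocks. Here the strata are very small and no restriction is named. The severity balance that the section sets out to obtain may not materialize.
- **Timing.** If the envelopes wait for the last baseline assessment of the whole cohort, the earliest T0 values are old when treatment starts, in patients who may still be recovering spontaneously. If each envelope is opened after its own participant's baseline, T0 is fresh, but allocation is sequential and the second problem applies.

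**Working it through.** **Inputs.** From Sequence generation {16a}: 39 patients, ratio 1:1:1, factors with 2, 2 and 3 levels. From Trial status: February to the end of April 2024. The relative sizes of the strata are not given, so equal likelihood is assumed and one skewed mix is tried.

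**1. The plan's own figures.** 2 × 2 × 3 = 12 subgroups, as stated. 39/3 = 13 per arm.

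**2. Stratum size.** 39/12 = 3.25 patients per stratum; 39/(12 × 3) = 1.08 per stratum-by-arm cell. With equally likely strata, about 4.3 of the 12 hold fewer than 3 patients, and about 8 of the 12 hold a number that is not a multiple of 3.

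**3. No restriction.** Each patient has probability 1/3 for each arm whatever the stratum, so unrestricted stratified allocation behaves exactly like simple randomization. P(13/13/13) = 39!/(13!)³ / 3³⁹ = 0.021. By simulation (400,000 runs) the mean gap between largest and smallest arm is 6.1.

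**4. Restricted schemes, patients allocated one at a time** (20,000 runs each):

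| Scheme | Exactly 13/13/13 | Arm gap 4 or more | Smallest arm 10 or fewer |
|---|---|---|---|
| Unrestricted | 2% | 76% | 57% |
| 12 equal strata, blocks of 3 | 10% | 27% | 8% |
| 12 equal strata, blocks of 6 | 5% | 52% | 27% |
| 3 equal Brunnstrom strata, blocks of 3 | 38% | 0% | 0% |
| 3 equal Brunnstrom strata, blocks of 6 | 23% | 5% | 0.5% |

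A skewed mix (assumed: sex 65/35, age 35/65, grade 30/40/30) changes little: with 12 strata the chance of a gap of 4 or more is 27% for blocks of 3 and 49% for blocks of 6.

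The zero for Brunnstrom-only blocks of 3 is structural. An unfinished block of 3 holds at most one patient per arm, so each stratum adds at most 1 to the difference between any two arms. Three strata add at most 3, whatever the mix of grades.

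**5. Severity balance.** Suppose the grades are equally frequent, so 39/3 = 13 patients per grade, or 13/3 = 4.3 per arm.

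- Unrestricted: the difference between two arms in the number of patients of that grade has SD √(13 × 2/3) = 2.9.
- 12 strata, blocks of 3: each grade spans 4 strata, so the difference can reach 4.
- Brunnstrom only, blocks of 3: the difference is at most 1.

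**6. Cost in precision.** Relative to 13 v 13, the standard error of a two-arm comparison is multiplied by √[(1/n₁ + 1/n₂)/(2/13)].

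- 10 v 16: √(0.1625/0.1538) = 1.028, or about 3% more.
- 9 v 17: √(0.1699/0.1538) = 1.051, or about 5% more.

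**7. Timing.** From 1 February to 30 April 2024 is 29 + 31 + 29 = 89 days, the longest wait for a first recruit if all 39 baselines must be complete before any envelope is opened.

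| Reading of Implementation {16c} | Balance | Age of T0 |
|---|---|---|
| Whole cohort first | All strata known in advance; 13/13/13 and near balance by stratum possible | Up to about 89 days |
| Each participant after own baseline | As in steps 3 to 5 | Fresh |

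Imbalance and an old T0 are therefore alternatives and do not add up.

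**The case against.** The best defence is that this is a condensed article. Block size is commonly left to the full protocol, and an external statistician oversees the sequence. A reader might infer that the trial uses no blocking and that equal arms will not be delivered. The text does not support that: it is silent on a within-stratum rule, and silence does not show that none exists. This part of the defence stands. It does not remove the contradiction between the two sections, and it does not rescue 12 strata under sequential allocation, because the block-of-3 and block-of-6 rows already grant a restriction.

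A reader might also infer that the trial suffers imbalance and an old baseline together, or that an old T0 biases the comparison between arms. Neither follows. The two arise under different readings of Implementation {16c}, and the individual envelopes of Concealment mechanism {16b} fit the per-participant reading. A wait that precedes allocation is unrelated to arm, so it adds noise and spontaneous recovery to change from baseline in all arms alike.

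Finally, exact 13/13/13 is a harsh yardstick, and a substantial loss of power cannot be claimed: the standard error rises only about 3 to 5% in the examples. With blocks of 3 in 12 strata, the smallest arm falls to 10 or fewer in only 8% of trials. This also stands. What is lost is mainly balance on severity, the stated purpose of the stratification.

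**Conclusion.** The point holds in a limited form and should be fixed before the first allocation.

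- **Contradiction between Trial design {8} and Sequence generation {16a}:** certain from the text; high confidence.
- **Thin strata:** if patients are allocated as they enter, the method as described does not secure 1:1:1 or severity balance. An arm gap of 4 or more has a chance of 76% with no restriction, 27% with blocks of 3 and about 52% with blocks of 6. The block figures assume 12 equally likely strata and barely move under the skewed mix tried. The consequence is weaker severity balance with about 13 patients per arm, and only a small loss of precision.
- **Envelope timing:** an ambiguity that needs resolving, with moderate confidence that it matters. On the literal reading the first T0 could be up to about 89 days old; on the per-participant reading the delay disappears and the thin-strata problem applies.

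**What to change.** 1. In Trial design {8}, delete the reference to simple random sampling and point to Sequence generation {16a}.
2. In Sequence generation {16a}, replace the 12-subgroup scheme with one method that suits 39 patients, and name the restriction. Either use minimization with a random element over sex, age group and Brunnstrom grade, or stratify by Brunnstrom grade only with permuted blocks.
3. In Implementation {16c}, state that each envelope is opened after that participant's own T0 assessment and before that participant's first session.

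**Cost.** A wording change and a new allocation list from the external statistician already foreseen, or a small script for minimization. Brunnstrom-only strata give up forced balance on sex and age. Fixed blocks of 3 balance best but are easy to predict where, as Who will be blinded {17a} concedes, the stimulation targets are visible; blocks of 6 are harder to predict and leave a gap of 4 or more in about 5% of trials. Minimization was not simulated here.

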**Methods:**

This study employs a double-blind, sham-controlled, randomized controlled trial design with a 2-week intervention period. Both participants and outcome assessors will remain unaware of treatment allocation throughout the study. Thirty-nine stroke patients will be recruited and randomized into three distinct groups, including the sham tACS group (SS group), the single-target tACS group (ST group), and the multi-target tACS group (MT group), at a 1:1:1 ratio. The primary outcomes are series reaction time tests (SRTTs) combined with electroencephalograms (EEGs). The secondary outcomes include motor evoked potential (MEP), central motor conduction time (CMCT), short interval intracortical inhibition (SICI), intracortical facilitation (ICF), magnetic resonance imaging (MRI), Box and Block Test (BBT), and blood sample RNA sequencing. The tACS interventions for all three groups will be administered over a 2-week period, with outcome assessments conducted at baseline (T0) and 1 day (T1), 7 days (T2), and 14 days (T3) of the intervention phase.

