## Statistical methods

### Statistical methods for primary and secondary outcomes {20a}

Statistical analysis will be performed using IBM SPSS Statistics 25 (http://www.spss.com.hk). Independent statisticians who remain blinded to the grouping will use an intention-to-treat (ITT) analysis approach to scrutinize the study results. In the case of missing data, the last observation value will be used for interpolation. Continuous variables conforming to a normal distribution will be described as the mean ± SD, while nonnormal distributions will be presented as medians, and the categorical variables will be described using frequency counts. The two-way variance with repeated measures will be performed for continuous variables that meet the assumptions of a normal distribution and homogeneity of variance, while the Wilcoxon test will be used if not. A chi-square test will be performed for categorical variables. The comparison between the three groups will use a two-tailed multivariate analysis of variance. When the *P* value was less than 0.05, the results were statistically significant. The post hoc comparisons will be performed by the Bonferroni correction for multiple comparisons if necessary.

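### Randomization is stratified by sex, age and Brunnstrom grade, but the named analyses include none of them; if the strata are balanced and prognostic, between-arm standard errors will be overstated

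*Protocol article*

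**What the plan says.** Sequence generation {16a} gives the size and ratio: "A total of 39 eligible participants will be assigned to three groups at a 1:1:1 ratio". The method named there is allocation "using stratified randomization with sex, age, and stroke severity as factors in this study". Patients are split by sex, then "the two groups will be grouped by age (< 60 and ≥ 60"), and then: "Lastly, the four groups will be grouped by Brunnstrom scale grade (III, IV, V), a total of 12 subgroups". The section says that this is meant to reduce bias. It gives no block size or other device that would force balance within a stratum.

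Trial design {8} describes the same 1:1:1 assignment differently: "as determined by a simple random sampling process".

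Statistical methods {20a} states: "The two-way variance with repeated measures will be performed for continuous variables" that meet normality and equal-variance assumptions, with a Wilcoxon test otherwise. For the arms it says: "The comparison between the three groups will use a two-tailed multivariate analysis of variance". It does not list the factors of the two-way model; group and time is the natural reading. No section puts sex, age or Brunnstrom grade into a model, and section {20b} plans no additional analyses.

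The abstract has "outcome assessments conducted at baseline (T0) and 1 day (T1), 7 days (T2), and 14 days (T3) of the intervention phase", so there are four visits.

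**The concern.** Stratifying on a factor that predicts the outcome makes the arms more alike on it, so the arm difference varies less from one possible randomization to the next. If the analysis leaves the factor out, its variance stays in the residual. The reported standard error then describes a less well balanced trial than the one that was run. Intervals are too wide and tests reject less often than their nominal 5% under the null.

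The main objective is whether multi-target stimulation does better than single-target. That is a between-arm question, and {20a} gives the three-group comparison to a between-patient method. The tasks are finger key presses and block transfer with the hemiplegic hand, so a link with upper-limb Brunnstrom grade is plausible, though the protocol does not assert one. With 13 patients per arm, lost precision is hard to recover.

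**Working it through.** **Inputs from the protocol.** N = 39 at 1:1:1, so 39/3 = 13 per arm. (Sample size {14} also gives 10 per group, which does not agree with 39; 13 is used here.) The strata reproduce as 2 sexes × 2 age bands × 3 grades = 12. That is 39/12 = 3.25 patients per stratum, or 3.25/3 ≈ 1.1 per stratum and arm. There are four visits.

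**Assumptions, not in the protocol.** R² for the three factors together, shown from 0 to 0.5. Allocation either simple, or in permuted blocks of 3 within strata. Outcome SD = 1, one value per patient, two-sided 5% test of one arm against another.

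**Step 1: baseline.** The group-only standard error should be about √(2/13) = 0.392. The simulated value at R² = 0 is 0.391.

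**Step 2: blocked stratified allocation, group-only model** (simulation, 4,000 to 6,000 runs per setting). Excess = reported SE / true SD of the estimate − 1.

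| R² | Reported SE | True SD | Excess | Type I error |
|---|---|---|---|---|
| 0 | 0.391 | 0.398 | none | 5.3% |
| 0.1 | 0.392 | 0.379 | 3% | 4.2% |
| 0.3 | 0.395 | 0.350 | 13% | 2.8% |
| 0.5 | 0.396 | 0.305 | 30% | 1.2% |

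Hand check at R² = 0.3: the critical value on 39 − 3 = 36 df is 2.028, and 2.028 × (0.395/0.350) = 2.289, which has a two-sided tail of 2.8%. At R² = 0.5, 2.028 × (0.396/0.305) = 2.633, with a tail of 1.2%. Both agree with the table.

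Perfect balance would give an excess of 1/√(1 − R²) − 1, which is 5%, 20% and 41% at R² = 0.1, 0.3 and 0.5. The simulated values are lower because many strata end in an incomplete block.

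**Step 3: the same trials with sex, age band and grade as main effects** (1 + 1 + 2 = 4 df).

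| R² | Mean 95% CI width, unadjusted → adjusted | Change | Power for a 1.2 SD difference |
|---|---|---|---|
| 0 | 1.586 → 1.614 | +2% | 84% → 83% |
| 0.1 | 1.589 → 1.530 | −4% | 85% → 87% |
| 0.3 | 1.600 → 1.348 | −16% | 86% → 94% |
| 0.5 | 1.607 → 1.143 | −29% | 89% → 99% |

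A separate simulation (8,000 trials per setting, true difference 1.0 SD) agrees: at R² = 0.3, type I error is 2.3% unadjusted and 4.7% adjusted, and power is 72% and 83%.

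**Step 4: all 12 cells instead** (11 df). The width is 1.685 against 1.586 unadjusted at R² = 0, and 1.596 against 1.589 at R² = 0.1. That is no gain at low R².

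**Step 5: simple allocation.** The group-only test has type I error of 4.5 to 5.1% at every R², so there is no miscalibration. Adjustment can still narrow intervals, but chance imbalance raises its price. The variance inflation is roughly (36 − 1)/(36 − 4 − 1) = 1.13, so the SE grows by √1.13 ≈ 1.06, and the interval is about 6 to 7% wider at R² = 0. With a width factor of about 1.067 × √(1 − R²), it gains once R² exceeds about 1 − 1/1.067² = 0.12.

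**Step 6: group-by-time.** This test uses each visit's deviation from the patient's own mean, so a stratum effect that is constant over visits drops out. On one simulated data set the F statistic was 1.204 both with and without such an effect. Only stratum differences in time course remain in its error term, and their size was not estimated.

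**The case against.** **Balance is not guaranteed.** No blocks are stated, the design section describes simple allocation, and there is about one patient per stratum and arm. This stands. It makes the calibration argument conditional and means that the allocation wording must be settled first.

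**R² is unknown, and the gain may be nil.** This also stands. At R² = 0 adjustment costs a little, and at 0.1 the gain is small.

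**Covariates may be left to an analysis plan that is not shown.** This stands in part. The section does not list model factors, so group and time is an inference. But it names its models, and a two-way ANOVA does not naturally hold three further factors. The point concerns a stated method, not a missing detail.

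**The repeated-measures test already removes constant stratum effects.** Correct for group-by-time. It does not help the group main effect, single-visit contrasts or the three-group MANOVA.

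A reader might infer that the error bars are certainly too wide and that the benefit of stratifying is thrown away. The protocol supports neither. The first needs enforced balance and prognostic factors. The second is wrong because the unadjusted estimate keeps its gain: its true SD falls from about 0.40 to 0.35 at R² = 0.3. Only the reported standard error and p-value fail to show it.

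**Conclusion.** The mismatch between allocation and analysis is real; its consequence is conditional. If strata are blocked and the factors are prognostic, between-patient arm comparisons are conservative by the amounts in Step 2, and main-effect adjustment restores their size and narrows the intervals. If allocation is simple, the unadjusted test is valid, and adjustment is worth having only if the factors explain more than a modest share of the variance. Group-by-time is touched only through differing time courses. Nothing here implies bias or excess false positives. The direction is firm; the size rests on the assumed R² and blocks of 3. It is a worthwhile, low-cost improvement in precision.

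**What to change.** 1. Reconcile Trial design {8} with Sequence generation {16a}: state whether allocation is simple or stratified and, if stratified, how balance within strata is produced.
2. In {20a}, add sex, age and Brunnstrom grade as main effects, not as 12 cells, to the parametric models for between-arm comparisons, and name the adjusted result as the primary estimate before unblinding.
3. Optional: enter age as continuous, and add a grade-by-visit term where several visits are modelled. The latter uses further degrees of freedom.

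The Wilcoxon fallback cannot take covariates, so this change does not cover it.

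Cost: wording only, since all three factors are known at randomization. The residual falls from 36 to 32 df. If the factors are not prognostic, the interval widens by about 2% under blocked strata, and by somewhat more under simple allocation (Step 5).
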